### Data Management and Quality Assurance

A comprehensive data management framework underpins the HDSS. Data capture uses an electronic system built on REDCap with a longitudinal, relational database structure designed for population surveillance. Each household is assigned a unique HHID and each individual an INDID, enabling linkage of demographic episodes, survey data, and clinical measurements to calculate person-time at risk and event rates. Field tablets store encrypted records locally during the day; at the end of each field shift, data are synchronized via secure, password-protected connections to a central cloud-based server hosted on institutional infrastructure. Built-in validation rules (range checks, mandatory fields, and cross-variable consistency checks) run at the point of entry, with additional automated scripts on the server to detect duplicates, outliers, and missingness. Data collectors receive intensive training on the electronic tools, household listing procedures, eligibility screening, physical measurements, point-of-care devices, ethics, and field record keeping, and they are supervised by field coordinators who conduct random spot checks and reinterviews for quality control. All equipment is calibrated regularly according to manufacturer recommendations, and standard operating procedures govern every step from mapping and enrollment to follow-up and data cleaning.

To maintain secure linkage between participant identity and the assigned INDID, a separate access-restricted identity register mapping personal identifiers (full name, date of birth, and sex) to the INDID is maintained on an encrypted, password-protected server, accessible only to the principal investigator and senior data manager. All analytical datasets contain INDIDs only, with no direct personal identifiers, ensuring participant confidentiality. At each follow-up visit, fieldworkers verify the participant’s name, date of birth, and household ID verbally before accessing their longitudinal record, confirming correct identity linkage.

### Data Analysis

The analytic plan encompasses descriptive statistics, robust prevalence and incidence estimations, and comparative analyses designed to quantify rural versus urban differences. Statistical software, primarily Stata (version 18; StataCorp LLC), will be employed. Numeric variables will be summarized using medians and IQRs, while categorical variables will be summarized using proportions. Logistic regression analyses (univariable and multivariable) will be used to identify and assess risk factors associated with NCDs, employing a hierarchical approach and stepwise backward elimination. The calculation of birth, mortality, prevalence, and incidence rates will be executed accordingly, and chi-square tests for trend will be used to analyze changes in NCD burden over time. Advanced statistical techniques, including regression and survival analyses, will facilitate robust estimation of NCD determinants and epidemiological transitions between the distinct study settings.

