**Methods:**

The HDSS uses a stratified multistage sampling design to recruit adults (aged ≥18 y) residing across 2 rural and 2 urban wards. Initial activities include comprehensive community profiling and household mapping, followed by a rigorous baseline survey, with systematic follow-ups scheduled every year. Data encompass essential domains such as vital events, migration patterns, detailed social determinants of health, health behaviors, self-reported and clinically assessed NCDs, physical examinations (including height, weight, blood pressure, and waist/hip circumference), biochemical markers (fasting glucose, lipid profiles, and urine sodium/creatinine), and standardized verbal autopsies. Data capture will make use of REDCap (Research Electronic Data Capture) to facilitate real-time data entry and validation. The protocol is underpinned by rigorous quality assurance procedures, continuous community engagement, and comprehensive ethical oversight.

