### Gaps in Existing Health Information Systems

Current surveillance systems suffer critical inadequacies that impede effective NCD response. Weak Civil Registration and Vital Statistics systems create fundamental gaps in understanding mortality dynamics, with many deaths occurring outside facilities and never recorded [11,12]. Facility-based surveillance captures only individuals accessing formal health care, systematically missing those who are undiagnosed, use traditional providers, or face access barriers [13]. This dramatically underestimates burden for NCDs with substantial asymptomatic populations [14]. Cross-sectional surveys cannot track longitudinal trends, assess incidence, or establish temporal relationships [15]. Self-reported data substantially underestimate NCD prevalence compared to biomarker measurement [14]. Systems lack the geographic granularity needed for targeted interventions [16].

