### Health and Demographic Surveillance Systems: A Solution

Health and demographic surveillance systems (HDSSs) provide continuous, longitudinal, population-based measurement of demographic, health, and social indicators within geographically defined populations [20,21]. HDSSs conduct regular household visits at intervals of 4 to 12 months, systematically updating births, deaths, migrations, and health events for all residents, enabling accurate calculation of rates and individual-level tracking over time [22]. This longitudinal design allows incidence assessment, prospective risk factor identification, intervention evaluation, and temporal trend monitoring that are impossible with cross-sectional surveys [15].

HDSSs differ fundamentally from other surveillance approaches in ways directly relevant to NCD monitoring. Unlike facility-based surveillance that captures only health care–seeking individuals, HDSSs conduct active community-based surveillance reaching all residents regardless of care-seeking behavior, health status, or socioeconomic position [11]. Unlike sentinel systems that monitor selected populations or facilities, HDSSs provide comprehensive data for entire defined populations, enabling unbiased prevalence and incidence estimation [23]. Unlike DHS, which provides periodic snapshots, HDSSs generate continuous real-time data enabling detection of emerging trends and rapid public health response [24].

Concrete examples demonstrate HDSS value for NCD surveillance. Verbal autopsies conducted in 6 eastern and southern African HDSSs revealed stable NCD mortality rates from 1995 to 2019 despite substantial declines in communicable disease mortality—epidemiological patterns that would be invisible to episodic cross-sectional surveys [25]. In rural South Africa, HDSS data showed that life-years lost to NCDs exceeded pre-HIV epidemic levels by 2014‐2018, demonstrating the system’s capacity to detect critical epidemiological transitions and inform policy priorities [19].

HDSSs employ standardized instruments ensuring data comparability across sites and over time [21], maintain population-based sampling frames covering all residents [20], and integrate multiple data sources, including household surveys, health facility records, and vital events registration [26]. They serve as platforms for nested studies, randomized trials, and intervention evaluations [27], generating evidence directly applicable to policy and practice.

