### Data Collection Methods

Baseline and subsequent follow-up rounds will be conducted via structured, interviewer-administered surveys using REDCap tablet-based electronic questionnaires. These instruments have been developed by adapting core modules from the WHO STEPS [30] and the standardized DHS tools of the INDEPTH Network [20], ensuring alignment with established population-based surveillance practice. Household-level forms are linked to each HHID and capture location geocoordinates (imported directly from the mapping module), asset ownership, housing conditions, water and sanitation status, and records of vital events (births, deaths, and in- and out-migrations) since the last round. Individual-level forms are linked via a unique individual identification (INDID) nested within each HHID and address core sociodemographic factors (age, sex, marital status, education level, and occupation), women’s empowerment, and exposure to gender-based violence. Health-related modules capture self-reported history of NCDs (hypertension, diabetes, and cardiovascular disease), mental health status, and key communicable diseases (HIV, tuberculosis, and malaria), as well as reproductive health metrics. For each reported condition, data are also collected on prior diagnosis by a health professional, current treatment status, and type of medication, enabling estimation of the diagnosis-treatment-control cascade for key conditions. Behavioral risk factors assessed include tobacco use, alcohol consumption, dietary patterns, physical activity, and sexual behavior, with skip patterns and range checks built into the electronic tools to minimize data entry errors. All items are drawn from, or adapted directly from, WHO STEPS and INDEPTH Network instruments that have been widely used and validated in demographic and health surveillance sites in sub-Saharan Africa, supporting their reliability and suitability for this target population.

The household questionnaire additionally captures individual-level items on mobile phone ownership (personal or shared), primary connectivity mode (SMS, mobile data, or Wi-Fi), and internet access, providing a baseline characterization of digital access at the household and individual levels to contextualize NCD communication and service delivery in both rural and urban settings.

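### The logistic risk-factor models do not separate previously diagnosed from newly detected cases, so baseline odds ratios for modifiable behaviours can be weakened, and unequally by site; a split by prior diagnosis is a cheap improvement

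*Protocol article*

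**What the plan says.** The Data Analysis section of the protocol article fixes the risk-factor method: "Logistic regression analyses (univariable and multivariable) will be used to identify and assess risk factors associated with NCDs". It adds a hierarchical approach with stepwise backward elimination. Later in the same section it says: "Advanced statistical techniques, including regression and survival analyses, will facilitate robust estimation of NCD determinants". Neither sentence defines the case group, the risk set or the timing of exposure relative to outcome.

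The data feeding these models are described elsewhere:

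- **Outcome.** The abstract's Methods list "self-reported and clinically assessed NCDs", so both known and survey-detected disease are captured.
- **Exposures.** Data Collection Methods states: "Behavioral risk factors assessed include tobacco use, alcohol consumption, dietary patterns, physical activity, and sexual behavior".
- **Diagnosis history.** For each reported condition, "data are also collected on prior diagnosis by a health professional, current treatment status, and type of medication". The only use given for these items is "enabling estimation of the diagnosis-treatment-control cascade for key conditions".
- **Timing.** Results puts baseline data collection at December 2024 (Mt Darwin) and March 2025 (Bindura), with baseline findings to be submitted by the end of 2026. The first follow-up is planned for the second quarter of 2027, subject to funding.

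The Introduction sets the standard. On surveys without follow-up it says: "Cross-sectional surveys cannot track longitudinal trends, assess incidence, or establish temporal relationships". Among the benefits of health and demographic surveillance systems in general it lists "prospective risk factor identification".

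**The concern.** A person told that they have hypertension or diabetes may cut salt, drink less, stop smoking or become more active. If the interview records current behaviour, that person enters the model as an unexposed case even though the exposure came before the disease. Pooling such cases with newly detected ones lowers exposure among cases and pulls the odds ratio toward 1. Backward elimination adds to the problem, because a weakened factor is more likely to be dropped from the final model.

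The size of the effect depends on the share of cases already diagnosed. The section on the burden of noncommunicable diseases says that many cases are undiagnosed and describes inadequate diagnostic capacity in rural areas. Anticipated Contributions and Impact again names delayed diagnosis as a rural problem. If the diagnosed share is higher in Bindura than in Mt Darwin, the same true association would look weaker in Bindura. A reader could take that artefact for a rural-urban difference in determinants, and the Conclusion names comparison of determinants between the sites as a purpose of the design.

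**Working it through.** The article states no figure on this point, so there is nothing to reproduce. The check has two parts.

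**1. Reading the sections together.** The models are for factors associated with NCDs. NCD status comes from self-report and from clinical assessment. The prior-diagnosis item has one stated use, the care cascade. The natural reading is therefore that known and new cases are pooled, although no sentence says so. Any such model run before the second quarter of 2027 has only prevalent cases available.

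**2. Size of the effect, by illustration.** All four inputs are assumptions; the article gives none of them.

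- p0 = exposure in non-cases = 0.30
- OR = true odds ratio = 1.5
- d = share of cases already diagnosed, varied over 0.20, 0.40 and 0.60
- q = fraction of exposed diagnosed adults who give up the exposure, central value 0.30

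Exposure in cases before any change:

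- odds(p0) = 0.30/0.70 = 0.4286
- odds in cases = 0.4286 × 1.5 = 0.6429
- p1 = 0.6429/1.6429 = 0.3913

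Observed exposure in cases is p1 × (1 − d × q), and the observed odds ratio is the odds of that divided by 0.4286. With q = 0.30:

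| d | d × q | Observed exposure in cases | Odds | Observed OR |
|---|---|---|---|---|
| 0.20 | 0.06 | 0.3678 | 0.5818 | 1.36 |
| 0.40 | 0.12 | 0.3443 | 0.5252 | 1.23 |
| 0.60 | 0.18 | 0.3209 | 0.4725 | 1.10 |

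Two sites with the same true odds ratio of 1.5, one with 20% and the other with 60% of cases diagnosed, would show 1.36 and 1.10.

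Range over q:

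- With q = 0.10, the three values are 1.45, 1.40 and 1.36.
- Over d from 0.20 to 0.60 and q from 0.20 to 0.40, the observed odds ratio runs from 1.40 (d = 0.20, q = 0.20) to 0.99 (d = 0.60, q = 0.40).

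**When would the direction change?** The observed odds ratio reaches 1 when p1 × (1 − d × q) = p0, that is, when d × q = 1 − 0.30/0.3913 = 0.233. At d = 0.60 this needs q of about 0.39. With q = 0.50, outside the range above, the values are 1.27, 1.06 and 0.88. With a true odds ratio of 2.0 and q = 0.50 they are 1.66, 1.37 and 1.11, with no reversal. With a true odds ratio of 1.3 and q = 0.30, d = 0.60 gives 0.97.

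**The case against.** The strongest reply is that the article does not state the flawed rule. It defines no model outcome, lists no covariates and nowhere says that diagnosed and new cases are pooled. A full protocol or analysis plan, not shown, could settle all of this. Results describes the baseline analysis as prevalence, risk-factor distributions and rural-urban comparisons and does not name a baseline logistic model. Survival analyses are planned for determinants, and Follow-Up Procedures provides for incidence and person-time at risk. The study aim on rural-urban differences concerns burden, exposure profiles, care-seeking, treatment access and outcomes, not odds ratios by site. Finally, restricting attention to newly detected cases brings its own selection: who is still undiagnosed depends on access to care, which may itself differ by site.

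Much of this stands. Pooling is the natural reading and not a stated rule, and a baseline logistic model is plausible but inferred. Three stronger readings that a reader might infer also go too far:

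- **That real risk factors will appear protective.** Over the assumed range the lowest value is 0.99, which is null. A clear reversal needs a weak true association, or more frequent behaviour change together with a high diagnosed share.
- **That treatment-affected lipids and glucose will distort the models.** The article does not say that biomarkers enter as predictors.
- **That the article contradicts its own criticism of cross-sectional surveys.** The logistic sentence speaks of association and makes no causal claim, and the remark about prospective identification describes such surveillance systems in general.

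The reply does not remove one point. The method is fixed down to its selection procedure, the item needed to guard against the problem is already collected, and the mention of survival analyses does not tie them to the risk-factor question or to exposures measured before onset.

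**Conclusion.** The point holds as a worthwhile, low-cost improvement and not as an error that undermines the design. For modifiable behaviours recorded as current, the logistic models as described can give weakened baseline odds ratios, and unequally weakened ones by site if the diagnosed share differs. The article supports the direction of that difference but gives no figure for it.

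The illustrated size, 1.36 against 1.10 for a true 1.5, rests on assumed values for exposure, true effect, diagnosed share and behaviour change. If few cases are diagnosed, or few people change, the loss is small: 1.45 with 20% diagnosed and 10% changing. The mechanism also assumes change away from the exposure; change in the other direction, or differential reporting, would act differently. Age, sex and education are not affected.

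**What to change.** Add to the Data Analysis section:

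1. Keep the all-cases logistic model. For modifiable exposures, add a prespecified multinomial analysis with three outcome categories: newly detected disease (meets the measurement definition, no prior diagnosis), previously diagnosed disease, and no disease. Use the prior-diagnosis item already in the questionnaire. The split suits hypertension and diabetes, for which blood pressure and fasting glucose are measured; a condition known only from self-report has no newly detected group.
2. Describe baseline odds ratios as cross-sectional associations.
3. From the first follow-up on, base claims about determinants, and about rural-urban differences in risk factors, on incident disease among adults free of it at the preceding round, with exposures measured at that round.

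The cost is analysis wording; no new data are needed. Each category has fewer cases, so intervals will be wider. The newly detected group is still prevalent, so it does not establish temporal order, and it is partly selected by access to care. It should therefore stand beside the all-cases model and not replace it as the sole main analysis.

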Within the 4 selected wards, all mapped households constitute the sampling frame, from which a systematic sample of households is drawn. Within each sampled household, all adults aged 18 years and older who meet the residency criterion are identified and invited to participate. Although the HDSS does not enroll every eligible adult resident because of resource constraints, this probability-based household sampling strategy, combined with formal power calculations, ensures that the resulting sample size is sufficient to address the primary study objectives. Using a baseline hypertension prevalence estimate of 30%, consistent with published data from Zimbabwe and comparable sub-Saharan African settings, a margin of error of ±2%, a 95% CI, and a design effect of 1.5 to account for household clustering, a minimum sample of approximately 3000 adults per site is required for robust prevalence estimation. This yields a total minimum analytical sample of 6000 adults across both rural and urban sites.

For the detection of a modest 2% absolute annual change in hypertension or diabetes prevalence (eg, from 30% to 32%) between surveillance rounds, with 80% statistical power and a 2-sided α of .05, a minimum of approximately 3500 participants per site per round is required. The estimated adult population across the 4 HDSS wards substantially exceeds this threshold, supporting the longitudinal objectives of the study. For rural-urban comparative analyses, equal allocation across the 2 sites provides 80% power to detect an absolute difference of 3% to 5% in key NCD outcomes. Subgroup analyses by sex, age group, and socioeconomic stratum are designated as exploratory, and appropriate corrections for multiple comparisons will be applied. Sample size calculations were performed in accordance with the WHO STEPwise approach to NCD risk factor surveillance (WHO STEPS) sample size guidance for population-based NCD surveys.

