### Follow-Up Procedures

Following the baseline census, longitudinal data collection rounds will be implemented annually over the 5-year surveillance period. Using the existing household and individual registers, field teams revisit each HHID and reverify the household roster, updating entries for births, deaths, in-migrations, out-migrations, and changes in marital status. Migration events are classified and dated using standard HDSS definitions, enabling calculation of person-time at risk and net migration rates. Migration events are identified and documented during each annual household roster update. New residents found in a previously mapped household who meet the standard residency criterion (at least 3 of the last 6 mo or intending to stay at least 6 mo) are classified as in-migrants, assigned a unique individual ID, and enrolled prospectively, with their origin and date of arrival recorded. Previously enrolled individuals confirmed by household members to have permanently departed the HDSS ward boundaries are classified as out-migrants, with their date of departure, destination, and reason for migration recorded and their follow-up record closed from that date, contributing person-time up to departure. Individuals who return after out-migration are reenrolled under their original ID, ensuring longitudinal continuity.

At each round, eligible adults are recontacted for updated interviews and measurements to estimate NCD prevalence and incidence, monitor changes in health-related behaviors and attitudes, and track risk factors over time. All recorded deaths are subjected to verbal autopsy using the WHO 2016 [31] standardized instrument administered on tablets; data are processed with automated cause-of-death assignment tools (eg, InterVA or InSilicoVA), given the limitations of vital registration in this setting.

Participant retention is managed through a structured recontact protocol whereby temporarily absent individuals receive at least 2 repeat visits at different times before being recorded as noncontactable for that round. At each round, the baseline characteristics of participants lost to follow-up will be compared with those retained to assess and account for potential attrition bias.

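### The chi-square test for trend assumes independent samples, but prevalence is measured each round largely in the same adults from fully enrolled households, so its error rate is not the nominal 5%

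*Protocol article*

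**What the plan says.** Data Analysis names the method for change over time: "chi-square tests for trend will be used to analyze changes in NCD burden over time". For risk factors it says "Logistic regression analyses (univariable and multivariable) will be used to identify and assess risk factors associated with NCDs", and it adds "Advanced statistical techniques, including regression and survival analyses" without further detail. It mentions neither repeated measurements nor household clustering.

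The design described elsewhere in the article is a linked cohort. Follow-Up Procedures states: "At each round, eligible adults are recontacted for updated interviews and measurements to estimate NCD prevalence and incidence". Returning out-migrants keep their original identifier, and Data Management and Quality Assurance describes linkage by household and individual identifiers. The cohort is open: in-migrants are enrolled and out-migrants' records are closed.

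Study Population and Sampling sets the household structure: "Within each sampled household, all adults aged 18 years and older who meet the residency criterion are identified and invited to participate". The prevalence sample size there includes "a design effect of 1.5 to account for household clustering". The same section aims to detect a change from 30% to 32% between rounds with about 3500 participants per site per round.

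**The concern.** The chi-square test for trend computes its variance as if each round were a fresh, independent sample. Two features of the design break this, in opposite directions. A person's hypertension status in one round predicts it in the next, so the change in prevalence varies less than the test assumes. People in one household resemble each other, so a round's prevalence varies more than the test assumes, and the change may too.

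At stake is the study's ability to detect the 2-point change it was sized for. The introduction justifies the system over repeated cross-sectional surveys because it follows individuals, yet the named trend test does not use that link. A reader also cannot tell from a p-value near 0.05 whether the true error rate is above or below 5%.

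**Working it through.** **Inputs from Study Population and Sampling.** Prevalence: "Using a baseline hypertension prevalence estimate of 30" percent. Precision: "a margin of error of ±2%, a 95% CI". Household design effect (DE) 1.5. Target change 30% to 32%. About 3500 per site per round. Two-sided α 0.05.

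**Assumed, because the article gives no value.** Within-person correlation ρ of the binary outcome between rounds, shown from 0.3 to 0.7.

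**1. The plan's own figures.**
- Prevalence sample: n = 1.5 × 1.96² × 0.3 × 0.7 / 0.02² = 1.5 × 2017 = 3025, matching the stated 3000 or so. Without the 1.5 it would be 2017, so the plan itself expects non-negligible household clustering.
- The 3500 does not reproduce for independent samples, which would need about 8394 per round. A paired formula with ρ about 0.58 and no design effect gives about 3525, but the article does not say that this was used. This is a separate matter. It explains why the independent-samples power below is 44% and not 80%.

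**2. Two rounds, same adults, no household design effect.** With two rounds the trend test reduces to the two-sample comparison.
- Assumed standard error: √[(0.30×0.70 + 0.32×0.68)/3500] = 0.01105, so d = 0.02/0.01105 = 1.809.
- With full overlap, true variance is close to (1−ρ) times the assumed variance. Write f = 1−ρ.
- Type I error of the named test: 2[1 − Φ(1.96/√f)].
- Power of the named test: Φ((d − 1.96)/√f).
- Power of an analysis with the right variance: Φ(d/√f − 1.96).

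| ρ | f | Type I error, named test | Power, named test | Power, linked analysis |
|---|---|---|---|---|
| 0 | 1.00 | 5.0% | 44% | 44% |
| 0.3 | 0.70 | 1.9% | 43% | 58% |
| 0.5 | 0.50 | 0.6% | about 41% | 73% |
| 0.7 | 0.30 | 0.03% | 39% | 91% |

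The named test's power hardly moves with ρ. What is lost is the gain that the linked data would give.

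As a check, a four-round trend test was simulated in about 3500 adults with strong persistence (latent correlation 0.8). Its type I error was about 0.1% to 0.4%, against 5.4% when the data were independent.

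**3. Household design effect of 1.5 also on the change.** Now f = 1.5(1−ρ), which equals 1 at ρ = 1/3.

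| ρ | f | Type I error, named test | Power, named test | Power, correct variance |
|---|---|---|---|---|
| 0.3 | 1.05 | 5.6% | 44% | 42% |
| 0.5 | 0.75 | 2.4% | 43% | 55% |
| 0.7 | 0.45 | 0.35% | 41% | 77% |

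Applying the full 1.5 to the change is an upper-end choice. A household effect that stays constant over time largely cancels from a within-person difference.

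**4. Partial overlap.** If a fraction v of adults is common to both rounds, the effective correlation of the two prevalences is about vρ. Take v = 0.7 for illustration; the article gives no retention figure. Then ρ of 0.3 to 0.7 becomes 0.21 to 0.49.
- Without a design effect: named test 43% to 42% power, correct variance 53% to 72%.
- With 1.5 on the change: type I error of the named test runs from 7.2% (f = 1.5 × 0.79 = 1.185) to 2.5% (f = 1.5 × 0.51 = 0.765).

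**5. Rural-urban contrast, conditional on no clustering adjustment.** Households lie wholly within a site, so the full design effect applies. Type I error = 2[1 − Φ(1.96/√1.5)] = 2[1 − Φ(1.600)] = 11.0%. Standard errors would be 1 − 1/√1.5 = 18% too small. At DE 1.2 the error is 7.4%, and at DE 2.0 it is 16.6%.

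**The case against.** **Silence on variance estimation is not an error.** The article says only that logistic regression will be used, ties no specific test to the rural-urban comparison, and condenses a fuller plan that is not shown. Survey commands or clustered errors may be specified there. This stands. A reader might infer that the logistic models and rural-urban tests will ignore clustering and exceed 5% error. The article does not say so, and the 11% holds only if no adjustment is made.

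**The size of the power loss depends on assumptions.** This also stands. If the effect is fixed at one that a correct analysis detects with 80% power, the formulas above give the named test 61% at ρ = 0.4 and 22% at ρ = 0.7. A reader might take those as the plan's loss. They are not evaluated at the plan's own sample size and target change, and they assume full overlap with no design effect on the change.

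**The direction is not certain.** Correct. A reader might infer that the trend test always loses power. With a design effect of 1.5 on the change and effective correlation below 1/3, it rejects slightly too often instead.

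**Disease burden covers more than prevalence.** For deaths and first diagnoses a person contributes at most one event, so the repeated-measures objection largely falls away, and survival analysis is also named. The point is therefore limited to prevalence trends.

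The stated method for those trends remains unanswered. The article names the chi-square trend test, so an analysis plan would have to contradict it, not merely add detail.

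**Conclusion.** The point holds for prevalence trends: the article fixes a test whose independence assumption its own design violates, so the actual error rate is not 5%. Under full overlap and no household design effect, the cost is 43% to 39% power against 58% to 91% over the assumed ρ of 0.3 to 0.7. Open-cohort turnover reduces that gap. A design effect on the change reduces it further and can reverse the direction when the effective correlation is below 1/3.

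For logistic regression and the rural-urban comparison the conclusion is conditional: household clustering assumed in the sizing needs to be carried into the analysis, and the article does not show whether it is. The 1.5 covers households only; correlation within the two wards per site would be additional.

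This should be corrected but does not undermine the study. The trend test is not designated as primary, no data collection is affected, and the first follow-up round is planned for the second quarter of 2027. The baseline rural-urban analysis is already underway, so the clustering question is the more urgent one.

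**What to change.** For prevalence trends, replace the chi-square test for trend with a marginal (GEE) or mixed logistic model. Include time from baseline, site and a site-by-time term, with variance clustered on household; because individuals are nested in households, this also covers repeats within a person. Measure time in calendar years: the first follow-up comes just over two years after baseline and later rounds are annual, so round number is not an evenly spaced scale.

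For baseline prevalence, rural-urban comparisons and risk-factor logistic models, state that household clustering is accounted for, through Stata's survey commands or cluster-robust variance with household as the unit.

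The cost is a change of wording and a few lines of code. The household and individual identifiers are already collected, Stata 18 is already named, and no new data are needed. The downside is somewhat wider cross-sectional intervals if the current intention was to ignore clustering.
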